### Data collection

Data will be collected at baseline (T0), after 2 weeks (T1) and every 3 months (T2,T3,T4), up to 12 months after the diagnosis (T5) (Fig. 2). If primary treatment is already completed before T3 (e.g. for patients with a melanoma who only undergo surgery), patients receive the questionnaires from T3 directly and after 3 months the questionnaires of T5. The remaining questionnaires will be omitted. Questionnaires will be sent by email to the participant. When the participant does not fill in the questionnaires within 1 week, the electronic systems sends the participants one reminder. If this does not lead to completing the missing questionnaire, the researcher contacts the participant by phone for a final request to complete the questionnaire.

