### Statistical analyses

All analysis will be performed following the intention-to-treat principle. Baseline characteristics will be shown by calculating means or medians for continuous variables and frequencies or percentages for categorical variables. Characteristics of patients who complete the study and patients who drop out, will be compared using T-tests for continuous variables and Pearson’s Chi-square analyses for categorical variables.

Linear regression analyses will be used for continuous variables adjusted for baseline variables (if measured at baseline) and treating hospital and cancer type. Mixed linear regression modelling adjusted for baseline variables as fixed factors (if measured at baseline) and stratification factors (treating hospital and cancer type) will be used to compare outcomes on repeated follow-up measurements T3 and T5. In these longitudinal analyses, the statistic model accounts for missing data based on the observed data [31]. Differential intervention effects due to sex (men/women), age (≤65/> 65 year), personality of type D (defined as 'scoring high on negative affectivity and social inhibition' [32]) (yes/no), type of cancer (breast/lung/colorectal/gynaecologic/melanoma), co-morbidity (none/1–2/> 3) and baseline levels of the outcomes of interest will be explored by adding interaction terms to the regression model.

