## Discussion

The aim of the GRIP study is to assess the effects of structured follow-up from primary care after the diagnosis of cancer on satisfaction and healthcare utilization of patients treated with curative intent. To optimise personalised cancer care for a growing patient population and for effective implementation of structured follow-up from primary care, policymakers and professionals need more information on the effects of structured and continuous primary care involvement in the cancer continuum. The GRIP study will provide evidence on the effects on patient satisfaction and healthcare utilization and secondary outcomes. In this pragmatic study, patients with multiple cancer types will be included aiming at high generalizability of the results. It will be explored whether there are subgroups of patients for whom this structured primary care works best.

In this protocol some choices were made, that need clarification. First, we chose to assess the addition of structured follow-up from primary care by a GP and HON to care as usual instead of substitution of the supportive care provided in hospitals. This choice was made because we believe it is not feasible nor desirable to completely replace supportive care provided from secondary care by that from the primary care team. In addition, we aim to test the assumption that additional care from primary care will lead to a shift of the utilised care from the secondary to the primary care setting.

Second, patient satisfaction and healthcare utilisation are chosen as primary outcomes, since these factors are considered most relevant from the perspective of patient and society. Third, for the secondary outcome ‘patient empowerment’, so far, no uniform definition and no unique measurement tools exist. Therefore, we chose to use two validated questionnaires (GSE and Pearlin Mastery Scale) to estimate the effect of our intervention on patient empowerment. Although in previous intervention studies during cancer treatment comparable numbers of questionnaires were acceptable, the use of several questionnaires might induce loss to follow-up.

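### The mixed model takes only T3 and T5 as outcomes, so its handling of missing data does not reach patients lost before T3, although questionnaires are sent to them at T0 to T2

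*Protocol article*

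**What the plan says.** All of the following is in the protocol article.

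- **Principle (Statistical analyses):** "All analysis will be performed following the intention-to-treat principle".
- **Longitudinal model (same section):** "Mixed linear regression modelling adjusted for baseline variables as fixed factors (if measured at baseline") and for the stratification factors, hospital and cancer type. It "will be used to compare outcomes on repeated follow-up measurements T3 and T5".
- **Missing data (same section):** "In these longitudinal analyses, the statistic model accounts for missing data based on the observed data".
- **Other model (same section):** "Linear regression analyses will be used for continuous variables adjusted for baseline variables (if measured at baseline) and treating hospital and cancer type". No time points are named for it.
- **Schedule (Data collection):** questionnaires go out at baseline (T0), at 2 weeks (T1) and then at three-monthly intervals (T2 to T4), with the last (T5) a year after diagnosis. If primary treatment is complete before T3, "patients receive the questionnaires from T3 directly and after 3 months the questionnaires of T5", and the other questionnaires are dropped.
- **Dropout:** the Sample size section allows 15%. The Discussion adds that "the use of several questionnaires might induce loss to follow-up".

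Which instrument is given at which visit is shown in Fig. 2, which was not available for this review.

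**The concern.** A likelihood-based mixed model uses incomplete records, but only from patients with at least one value on the outcome side. Here baseline is on the covariate side and the outcome side holds T3 and T5. Someone who leaves after T0, T1 or T2 therefore supplies no row. For that patient the observed data that the missing-data sentence relies on are not in the model, even though up to three questionnaires may have been returned.

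The trial is unblinded and satisfaction is self-reported, so loss related to how care is going, and differing by arm, is plausible. If such loss is predicted by T1 or T2 answers and not fully by the model's covariates, the T3 and T5 comparison is biased, and the information that could reduce the bias has been left out.

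**Working it through.** **1. The plan's own sample size.** Inputs from Sample size: effect 0.5 SD, power 0.8, alpha 0.05 (two-sided reproduces the figure), dropout 15%. The two-sample t-test solution is 63.77, so 64 per group, as stated. Inflation gives 64 / 0.85 = 75.3. The plan states 75, and 75 × 0.85 = 63.75, so the figure is reproduced to within one patient.

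**2. Who enters the mixed model.**

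| Questionnaires returned | Outcome rows | In the model? |
|---|---|---|
| T3 and T5 | 2 | yes |
| only one of T3 and T5 | 1 | yes |
| T0, T1 or T2 only | 0 | no |

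In a simulated trial of 150 with 20 patients leaving before T3, the T3/T5 model used 150 − 20 = 130 patients. With T2 added as an outcome it used all 150.

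**3. How many could be affected.** The upper limit is 0.15 × 150 = 22.5, about 11 per arm. It requires the whole planned dropout to fall before T3; the article gives no timing.

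**4. Precision (t-test power at 0.5 SD).**

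| Share of the 15% lost before T3 | Left per arm | Power |
|---|---|---|
| none | 75 | 0.860 |
| half | 75 − 5.625 = 69.375 | 0.833 |
| all | 75 − 11.25 = 63.75 | 0.800 |

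The allowance covers the loss of precision even in the last row.

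**5. Possible bias, illustrative.** None of these assumptions is in the article: outcome measured at T0, T2 and T3; correlation 0.6 between visits; true effect 0.50 SD at T2 and T3; 15% lost before T3 in each arm; where loss depends on T2, a logistic slope of 1 per SD.

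| How loss depends on the T2 score | Baseline-adjusted T3 estimate | Estimate using T2 |
|---|---|---|
| low scorers leave, control arm only | about 0.46 | 0.50 |
| low scorers leave, intervention arm only | 0.53 | 0.50 |
| opposite directions (low scorers leave control, high scorers leave intervention) | 0.43 | 0.50 |

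A second simulation of the control-arm case (correlation 0.5, average of T3 and T5, 14 to 15% loss per arm, 1,000 trials) also gave 0.46 without T2 and 0.50 with it. Reversing both directions in the last row reverses the shift: 0.50 + (0.50 − 0.43) = 0.57. If the dependence is the same in both arms the shifts roughly cancel (−0.04 + 0.03). If loss depends only on covariates already in the model, the bias is nil.

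**6. Scale.** With 64 per arm and correlation 0.6, the standard error of the adjusted difference is √(2/64 × (1 − 0.6²)) = 0.14 SD. Shifts of 0.03 to 0.07 SD are one fifth to one half of that.

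**The case against.** The strongest reply has five parts.

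- **A reader might infer that the intention-to-treat principle fails.** The article does not support that. Nothing in it analyses patients other than as randomised, and a likelihood model on observed outcomes is valid if loss depends only on what the model contains. What stands is narrower: not every randomised patient enters this model.
- **A reader might infer that early dropouts contribute nothing to the trial's results.** That is also unsupported. The separate linear regressions have no stated time points and may use T1 or T2 outcomes. The exclusion is shown for the T3/T5 mixed model only.
- **The early data may not include the outcome.** The schedule by instrument is in the unseen Fig. 2, and the qualifier about measurement at baseline implies that instruments differ by visit. If an outcome is collected only at T3 and T5, no earlier value of it has been ignored. This objection stands and decides which fix applies to which outcome. The other early questionnaires could still serve as predictors.
- **Loss before T3 may be small.** The Discussion says only that loss might occur, and notes that similar questionnaire loads were acceptable in earlier studies. Data collection provides a reminder and a telephone call. Patients who finish treatment early go straight to T3 and are not early losses. All of this stands.
- **Sensitivity analyses may be in the full protocol or analysis plan.** They may, and their absence here is not the point. The article itself fixes the modelled visits and makes a positive statement about missing data that is wider than that model supports.

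**Conclusion.** The point holds in a limited form. As specified, the mixed model excludes patients with neither T3 nor T5, and the missing-data sentence is correct only for patients with at least one of the two. For those lost earlier, at most about 22 of 150, validity rests on loss depending only on arm, baseline (for outcomes that have a baseline value), hospital and cancer type.

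Power is not the problem. Bias is possible, but the article gives no means of estimating it, and the illustrative shifts can go either way and are smaller than the standard error. They do not show that the planned estimate is biased. They show that it depends on an assumption which data already scheduled for collection could weaken. This is a worthwhile improvement to a stated method, not a flaw that invalidates the trial.

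**What to change.** 1. Keep the T3 and T5 contrasts as the quantities of interest.
2. Where the outcome is also collected at T1 or T2, add those visits as outcomes with visit-by-arm terms, and read the contrasts at T3 and T5. Treat visits omitted under the early-completion rule in Data collection as missing by design.
3. Where the outcome is collected only at T3 and T5, add an analysis of all randomised patients using multiple imputation by arm, with the T0 to T2 questionnaires, hospital and cancer type as predictors.
4. Reword the missing-data sentence so that it applies to patients with at least one modelled outcome, and say that patients with neither T3 nor T5 do not enter the mixed model.

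Cost: a little more analysis work and some care with the visits omitted by design. With 75 patients per arm the imputation model has to stay modest, so the predictors should be few and chosen in advance. No new data collection is needed.

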### Inclusion criteria

Patients are eligible for study participation, when they meet all of the following criteria:Newly diagnosed with one of the following types of cancer: breast cancer, colorectal cancer, all types of gynaecologic cancers, lung cancer or melanoma. Not being recurrent disease.Cancer therapy is initiated with curative intent (cancer staged I-III).Patient’s general practitioner agrees to participate in the GRIP-study.Patient is 18 years or older.Patients can be included before start of the cancer treatment.Sufficient mastery of the Dutch language or translator available during study.

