### Recruitment and allocation

To ensure reaching the required sample size of 150 patients, we involved all three major hospitals (one academic and two-non-academic) located in the greater urban region of Utrecht, the Netherlands, in the study. In addition, researchers will visit all sites biweekly to motivate the sites for inclusion of patients. All four GP cooperative care organisations in the region, together representing 300 GPs, and two home care organisations employing primary care oncology nurses, participate in the study. The GP cooperative care organisations inform their member GPs about the GRIP study, and the GPs can decline to collaborate by opt-out.

Eligible patients will be recruited in the hospital by the treating physician or oncology nurse after the patient is informed of his/her cancer diagnosis. After verbal consent, the treating physician or oncology nurse informs the research team, who contacts the patient by phone the (working)day after diagnosis. Written informed consent is obtained from all participants by the researcher.

The researcher will randomise the participants to intervention or usual care by using an computer operated electronic randomisation module, which is designed and maintained by the independent data management department of the UMC Utrecht. For randomisation, gender, date of birth, study number and site of inclusion of the patient need to be filled in on the website. Minimisation is applied to ensure balance between groups in treating hospital and cancer type. Due to the nature of the intervention, patients and health care providers are not blinded.

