### Sample size

We assumed a medium effect size (0.5) to be a clinically relevant difference in patients’ satisfaction between the two study groups. Using a power of 0.8 and an alpha less than 0.05, at least 64 patients per study group are required. Accounting for an estimated dropout of 15%, 75 participants in each group are needed.

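### Age enters the exploratory interaction model only as a split at 65, although date of birth is recorded for every patient; this loses information if benefit changes gradually with age

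*Protocol article*

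**What the plan says.** The section Statistical analyses lists the characteristics by which the intervention effect may differ. Age is among them, as "age (≤65/> 65 year". Differential effects "will be explored by adding interaction terms to the regression model", so the split is a term in the model and not only a way of laying out a table. Baseline values of the outcomes are listed in the same sentence without any categories.

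The section Recruitment and allocation states: "For randomisation, gender, date of birth, study number and site of inclusion of the patient need to be filled in on the website". Exact age is therefore known for all randomised patients. The only age limit under Inclusion criteria is "Patient is 18 years or older". The article gives no expected mean, spread or share of patients over 65, and no rationale for the cut.

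**The concern.** A two-group term assumes that benefit is constant up to 65, jumps there, and is constant afterwards. It treats a patient of 30 and one of 65 as alike, and patients of 65 and 66 as different. Nothing in the article argues for that shape. If benefit rises or falls gradually, the split uses only part of the available contrast in age, and a real trend is more easily missed.

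The Discussion says the trial will look for patient groups in whom structured primary care works best, and the Background motivates the study partly by population ageing. Age is therefore a natural candidate modifier. The trial is sized for a main effect only, so interaction tests start out weak. A null result from a test weakened further could be misread as evidence of equal benefit at all ages.

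**Working it through.** **The article's own figure.** Inputs from Sample size: a standardised effect of 0.5, power 0.8 and alpha 0.05, from which the article derives 64 per group; a 15% allowance for dropout then brings this to 75. With two-sided alpha 0.05, n per group = 2(1.960 + 0.842)²/0.5² = 62.8, or 63 by the normal approximation. The t-based calculation gives 63.77, so 64, as stated. 64/0.85 = 75.3, against 75 stated. The figure reproduces, but it concerns the main effect. The article gives no figure for any interaction.

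**Information kept by the split.** Assume (not in the article) that age is normal and the interaction linear in age, with 1:1 allocation. Let z = (65 − mean)/SD and p = share over 65. The fraction of information kept is the squared correlation between age and the two-group indicator:

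r = φ(z)² / [p(1 − p)]

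- Mean 65, any SD: z = 0, φ = 0.3989, p = 0.50; r = 0.1592/0.25 = 0.637. Loss 36%.
- Mean 60, SD 12: z = 0.417, φ = 0.3658, p = 0.339; r = 0.1338/0.2239 = 0.598. Loss 40%.
- Mean 58, SD 11: z = 0.636, φ = 0.3258, p = 0.262; r = 0.1062/0.1935 = 0.549. Loss 45%.

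Over means 58-65 and SDs 11-13 the loss is thus 36-45%.

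**Wider assumptions.**

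- Normal age, mean 55, SD 10: z = 1, p = 0.159, r = 0.439. Loss 56%.
- Uniform age, where r = 3p(1 − p): over 45-85, p = 0.50 and r = 0.75, loss 25%; over 30-85, p = 0.364 and r = 0.694, loss 31%.

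The range is about 25-56%.

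**Power.** With 128 evaluable patients (2 × 64), residual SD 1 and age in SD units, the standard error of the interaction is about 2/√128 = 0.177. Power of 80% on continuous age needs a slope of 2.80 × 0.177 = 0.495 SD of outcome per SD of age. The split multiplies the noncentrality by √r:

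- r = 0.549: 2.80 × 0.741 = 2.075; power = Φ(2.075 − 1.960) = 55%.
- r = 0.637: 2.80 × 0.798 = 2.235; power = Φ(2.235 − 1.960) = 61%.

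A simulation (4,000 runs, N = 128, slope 0.495) gave, for continuous age against the split, 0.78 against 0.58 with 50% over 65, 0.77 against 0.55 with 35%, and 0.78 against 0.49 with 25%. The simulated loss is somewhat larger than the formula's.

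**Smaller interactions.** A slope of 0.495 per SD of age is about as large as the whole assumed main effect of 0.5. For smaller slopes, with the same r of 0.549-0.637:

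- 0.20: noncentrality 0.20/0.177 = 1.13; power about 20% continuous, 13-15% split.
- 0.25: noncentrality 0.25/0.177 = 1.41; power about 29% continuous, 18-20% split.

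**The case against.** The analysis is exploratory. Age modification is not part of the aim, the outcomes or the sample size, and no stated conclusion rests on it. At interaction sizes smaller than the main effect, either coding would usually miss the effect, so the drop from 80% to 55-61% flatters the practical gain. All of this stands, and it keeps the point minor.

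The choice of shape also cuts both ways. The loss is a squared correlation, so it is symmetric: if the effect truly stepped at 65, the split would lose nothing, and a straight line in age would lose the same 36-45%. A check for curvature costs a further parameter in a small sample. A reader might infer that continuous age is better whatever the truth, or comes free of any downside; that does not follow. What remains is that the article offers no reason to expect a step at 65, and that a continuous term with a curvature check, shown beside the two-group display, covers both possibilities better than the split alone.

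A reader might also take a loss of about 40% as established. It is only a central value under assumed normal age and a linear interaction. The article supplies neither the age distribution nor the shape of the effect.

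**Conclusion.** The point holds as a minor one. The article fixes an unexplained cut of a modifier that is known exactly for every patient, inside the model that is meant to test it. Under a linear interaction and normal age with mean 58-65 and SD 11-13, the cut loses about 36-45% of the information on an age trend; across wider age distributions the loss is roughly 25-56%. Power of 80% on continuous age becomes about 55-61%. Under a true step at 65 the loss is nil.

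One might go further and infer that the trial's findings on satisfaction or utilisation are weakened. The text does not support that: the split appears only in the exploratory interaction terms, and the primary comparison does not depend on it. Nor would continuous age make the interaction test well powered.

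**What to change.** In Statistical analyses, replace the two-group age term with continuous age as the modifier: linear, with a check for curvature. Report the estimated intervention effect, with confidence intervals, at for example 55, 65 and 75 years. Keep the split at 65 as a descriptive display, so that an apparent step there would still be visible.

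This needs no new data, patients or procedures, only a change of analysis wording. The small downsides are less sensitivity to a true step at 65 and one extra parameter for the curvature check. If there is a substantive reason to expect a step at 65, state it instead.

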**Fig. 2 Fig2:**
[figure not shown]
Questionnaire timeline in the cancer care pathway. GP General Practitioner; EORTC QLQ-c30 European Organisation for Research and Treatment of Cancer Quality of life Questionnaire; GSE General Self-Efficacy Scale; MHI-5 Mental Health Inventory; PEPPI Perceived Efficacy in Patient-Physician Interactions; SDM-Q9 Shared Decision Making Questionnaire; iMTA PCQ Productivity Cost Questionnaire of the institute for Medical Technology Assessment; DS-14 Assessment of negative affectivity, social inhibition, and Type D personality; EORTC-info 26 European Organisation for Research and Treatment of Cancer Assessment Satisfaction with information; iMTA MCQ Medical Cost Questionnaire of the institute for Medical Technology Assessment; EORTC-IN-PATSAT Satisfaction with care questionnaire; NRS Numeric Rating Scale

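### Effect modification by personality is explored only through Type D yes/no, so a graded modification is detected less often and a Type D interaction cannot be told apart from modification by one trait

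*Protocol article*

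**What the plan says.** In the protocol article, Statistical analyses, the personality modifier is given with its definition and levels: "personality of type D (defined as 'scoring high on negative affectivity and social inhibition' [32]) (yes/no"). A patient counts as yes only when both traits are high. It stands in a list with sex, age, cancer type, co-morbidity and baseline outcome levels; the last of these has no stated categories. Differential effects "will be explored by adding interaction terms to the regression model".

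The Fig. 2 legend describes the instrument as "DS-14 Assessment of negative affectivity, social inhibition, and Type D personality", so it covers both traits as well as the class. No arm-by-trait term appears anywhere in the article.

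The Discussion gives the purpose: "It will be explored whether there are subgroups of patients for whom this structured primary care works best". The Sample size section covers only the main satisfaction comparison: "We assumed a medium effect size (0.5) to be a clinically relevant difference".

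**The concern.** Collapsing two trait scores into one indicator has two consequences.

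1. **Loss of gradation.** Patients high on negative affectivity only, high on social inhibition only, and high on neither are all coded no. If benefit changes steadily along one trait or along the sum, the indicator carries only part of that signal.
2. **No attribution.** Type D patients are high on negative affectivity by definition, and likewise on social inhibition. Modification by one trait alone will therefore show up as an arm-by-Type D interaction, and no other term in the stated model can reveal this. This follows from the definition and needs no numerical assumption.

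At stake is how an exploratory result is read. A null Type D interaction would be weak evidence against modification by personality, and a positive one could be described as a Type D effect without the means to check it.

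**Working it through.** **The plan's own figures.** "Using a power of 0.8 and an alpha less than 0.05, at least 64 patients per study group are required". For a standardised difference of 0.5, two-sided alpha 0.05 and power 0.8, the normal approximation gives n = 2(1.96 + 0.84)²/0.5² ≈ 62.8, so 63 per group. The t-test version gives 63.8, so 64. The article does not state sidedness; two-sided reproduces the figure and one-sided would give 50. "Accounting for an estimated dropout of 15%, 75 participants in each group are needed". Here 64/0.85 = 75.3, which agrees with 75 to within rounding. The evaluable number used below is 2 × 64 = 128. No power is stated for any interaction.

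**Inputs not in the document (assumed).** Two normal trait scores with correlation 0.2 to 0.6, a common cut on both, and 15-30% Type D (20% for the power runs). Simulated trials had 1:1 allocation, residual SD 1, main effect 0.5 SD and alpha 0.05.

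**Step 1: information kept.** The share of a linear modifier's variance that an indicator keeps is the squared correlation between the two.
- Modification linear in negative affectivity: 22-43% kept.
- Modification linear in the sum of the scores: 36-53% kept.
- Patients high on negative affectivity only, hence coded no: 12-22% of the sample.

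**Step 2: rough power check.** With balanced arms and residual SD 1, the variance of an interaction slope per SD of modifier is 4/n = 4/128 = 0.031. For 0.4 SD per SD, the non-centrality is 0.4²/0.031 ≈ 5.1. If negative affectivity is the modifier, the indicator retains 0.22 to 0.43 of this, about 1.1 to 2.2.

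**Step 3: simulated detection rates (n=128, 20% Type D).**

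| True modification | Type D yes/no | Joint 2-df test, both continuous scores by arm |
|---|---|---|
| None | about 5% | about 5% |
| 0.4 SD per SD of negative affectivity | 18-25% | 47-49% |
| 0.4 SD per SD of the sum | 28-30% | 47-49% |
| 0.2 SD per SD of negative affectivity | 8-10% | 15% |
| Both-high group only, 1.0 SD difference from others | 57-61% | 22-25% |
| Both-high group only, 0.4 SD difference from others | 15-16% | 7% |

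The scale of the last two rows needs care. At 20% prevalence the SD of the indicator is √(0.2 × 0.8) = 0.4, so 0.4 SD of outcome per SD of the indicator equals 0.4/0.4 = 1.0 SD between Type D and other patients. A true 0.4 SD difference is the final row.

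**Step 4: attribution.** When negative affectivity alone modifies the effect at 0.4 SD per SD, the unadjusted Type D interaction is significant in 18-25% of trials. With both score-by-arm terms in the model, this falls to about 5%, the null rate.

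**Step 5: different assumptions.** With correlation 0.2-0.5 and cuts 0.25-0.75 SD above the mean (7-24% Type D), the indicator keeps 15-36% (negative affectivity) or 24-48% (sum). At 0.5 SD per SD of negative affectivity, yes/no detects 17-38% and the separate continuous negative affectivity term 66-77%. If the sum drives modification at the same size, each separate trait term detects only 27-42%, no better overall than 26-46% for yes/no, whereas a term for the sum itself detects 78-80%. Testing the traits one at a time is therefore not a sufficient remedy, and a joint test is needed.

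**The case against.** Type D is a deliberate, cited construct, defined in the article as "scoring high on negative affectivity and social inhibition". If the question is whether that type modifies the effect, a yes/no term answers it directly, and it is the stronger test when modification really is confined to the both-high group. Which test wins depends on an unknown truth. This stands, and it is why the indicator should stay.

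The analysis is exploratory, and the assumed 0.4 SD per SD is large: against a main effect of 0.5 it puts the benefit at 0.1 at one SD below the trait mean and 0.9 at one SD above. At 0.2 SD per SD neither test has useful power, and the chief limit is a trial not sized for interactions. This also stands.

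A separate analysis plan, not shown here, might add continuous scores, and nothing in the article forbids it. That is fair, but the article does fix the coding of this modifier rather than leaving it open, so the point can be raised on its text.

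A reader might go further and infer that the yes/no coding is an error, or that it would direct the intervention to the wrong patients. The article supports neither: it states no plan to select or treat patients on this result. A reader might also infer that graded modification is mostly lost whatever the data look like. The article gives no trait correlation, cut-off or prevalence, and in one assumed corner (sum-driven, correlation 0.6, 30% Type D) slightly more than half is kept.

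Finally, it is tempting to allow a Type D claim only if the adjusted term stays significant. That rule would miss a genuine effect confined to Type D in about 60-65% of trials even at a 1.0 SD difference.

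**Conclusion.** The point holds as a limited one. By construction, the stated model cannot distinguish a Type D effect from modification by a single trait. For modification graded in one trait or in the sum, the indicator is the weaker test: at 0.4 SD per SD its detection rate is roughly 40-65% of that of the joint test (18/47 = 0.38 to 30/47 = 0.64). At half that interaction size both tests are poor. For modification confined to the both-high group the ordering reverses. The attribution problem needs no assumption, whereas every detection rate rests on assumed trait distributions, correlation, prevalence and interaction size. Only an exploratory analysis is touched. No primary or secondary conclusion, and no part of the sample size, changes.

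**What to change.** In Statistical analyses:
- Keep arm-by-Type D (yes/no) as the pre-specified personality term.
- Add one exploratory model with the continuous DS-14 negative affectivity and social inhibition scores as main effects and as arm interactions, with a joint 2-df test of the two interactions.
- Also report the arm-by-Type D estimate and confidence interval with both score-by-arm terms included. Judge specificity to Type D from estimates and intervals, not from whether the adjusted term stays significant, because its power is low.

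The cost is a sentence or two of analysis wording and one additional model, using an instrument already in the questionnaire set. The downside is a few more exploratory tests and wider intervals in the combined model.

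### The co-morbidity categories for the exploratory interaction analysis leave a count of exactly three without a category

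*Protocol article*

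**What the plan says.** In Methods, Statistical analyses, the protocol article names six kinds of possible effect modifier: sex, age, type D personality, cancer type, co-morbidity, and the baseline level of the outcome. Differential effects across these "will be explored by adding interaction terms to the regression model". Most factors are given with their categories. Age is "age (≤65/> 65 year", which covers every age. Co-morbidity is "co-morbidity (none/1–2/> 3".

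No other part of the article gives a different co-morbidity grouping or says where a patient with three conditions belongs. The Discussion confirms the exploratory purpose: "It will be explored whether there are subgroups of patients for whom this structured primary care works best".

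**The concern.** A categorical modifier has to give each patient exactly one level. The printed co-morbidity factor does not, because its middle level ends at two and its top level starts above three.

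There are two possible consequences. If the levels are programmed as printed, a patient with three conditions has a missing value on this factor, and an ordinary regression with that interaction leaves the patient out. The mixed model's treatment of missing data does not obviously help, since it concerns follow-up measurements and not a covariate level that was never defined. If the analyst notices the gap, the patient must be assigned to a level, and unless this is settled beforehand the choice is made with the data at hand. Either way, the co-morbidity subgroup result depends on something the plan has not fixed.

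**Working it through.** **The plan's own figure.** The only calculated figure in the article is the sample size. It matters here only as the source of the denominator.

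- Inputs (Sample size section): standardised difference 0.5, power 0.8, alpha 0.05 (taken as two-sided), dropout 15%.
- The exact two-sample t-test calculation gives 63.77 per group, rounded up to 64; power at 64 per group is 0.801. This agrees with "Using a power of 0.8 and an alpha less than 0.05, at least 64 patients per study group are required".
- Dropout: 64 / 0.85 = 75.3, and 75 × 0.85 = 63.75. The stated 75 per group is reproduced to within rounding. Two groups give 2 × 75 = 150.

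**Are the categories exhaustive?** Each count was assigned to the levels as printed, and then to the levels under two repairs.

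| Number of conditions | As printed: none / 1–2 / >3 | Repair A: none / 1–2 / ≥3 | Repair B: none / 1–3 / >3 |
|---|---|---|---|
| 0 | none | none | none |
| 1 | 1–2 | 1–2 | 1–3 |
| 2 | 1–2 | 1–2 | 1–3 |
| 3 | **no level** | ≥3 | 1–3 |
| 4, 5, 6 | >3 | ≥3 | >3 |

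Three is the only gap, and no count falls in two levels. Each repair gives every count exactly one level, but a patient with three conditions is in the top group under A and in the middle group under B.

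**How many patients?** The article gives no co-morbidity distribution, so the share p with exactly three conditions is an assumption. Number without a level = 150 × p:

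- p = 2%: 150 × 0.02 = 3
- p = 5%: 150 × 0.05 = 7.5
- p = 10%: 150 × 0.10 = 15
- p = 15%: 150 × 0.15 = 22.5

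These are counts at randomisation; dropout would lower them. The true share may lie outside this range.

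**What depends on the factor?** The main linear and mixed models adjust for baseline values, treating hospital and cancer type. Co-morbidity appears only in the list of interaction terms. The sample size uses none of the modifiers.

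**The case against.** The strongest reply is that this is a slip for ≥3, that any analyst would read it so, and that nobody would then be lost. A slip is indeed the likely cause. It is less likely to come from the conversion of the text, because the inclusive sign is printed correctly for age in the same sentence, although this cannot be excluded. But the intended reading is an inference: repair B also fits the text, and the two differ for exactly the patients at issue.

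A second reply is that the coding of an exploratory covariate is normally settled in an analysis plan, which may exist and is not shown. That would be an answer if the article had left the categories out. It states them, and as stated they do not work. The reply does weaken any prediction that patients will actually be lost.

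Three stronger readings are tempting, and the document does not support them.

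- *Patients with three conditions will be dropped.* The article contains no exclusion rule. Loss is only what follows if the levels are coded literally.
- *Intention to treat is breached.* The article says "All analysis will be performed following the intention-to-treat principle", but that principle concerns analysing patients in the arm to which they were randomised. A missing value on one exploratory modifier does not change that.
- *The high co-morbidity group is thinned.* This presumes that ≥3 was meant. Under repair B these patients belong to the middle group, and nothing in the article shows which group is smallest.

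**Conclusion.** The point holds in a narrow form. The printed co-morbidity levels are not exhaustive, and the place of a patient with exactly three conditions is undefined. This follows from the text alone and needs no assumption.

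The size does need one. Across assumed shares of 2% to 15%, between 3 and about 22 of the 150 planned patients would have no level; the article offers nothing to narrow that range. The importance is low, because only one exploratory modifier is affected. No conclusion about the main effect of the intervention, no other subgroup analysis and no sample size figure changes.

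**What to change.** Before analysis, restate the co-morbidity levels in the protocol or analysis plan so that every count has exactly one place, for example none / 1–2 / ≥3. If none / 1–3 / >3 was intended, say so instead; what matters is that one of them is fixed before the data are examined by arm. If an existing analysis plan already has exhaustive levels, a reference to it is enough.

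Entering the number of conditions as a continuous modifier would also avoid the gap, but it assumes a linear change in effect per condition and is not needed to solve the problem.

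The cost is one corrected sign. No data collection, sample size or other analysis is affected.
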